### Study treatments

Baseline evaluations will be performed as close as possible to, and within 30 min before, administration of initial study medication. Patients will be randomly assigned to receive either inhaled loxapine 10 mg (delivered dose 9.1 mg) using the hand-held, portable, *Staccato* delivery system or IM aripiprazole 9.75 mg per 1.3 mL dose. Patients will receive a maximum of 2 doses of either study drug with the second dose given if required at least 2 h after the first dose.

Randomisation will be achieved using an interactive voice response system and will be stratified according to the patient’s disease type (schizophrenia or bipolar I disorder).

The planned duration of participation in the study will be up to approximately 30 h consisting of a screening and baseline phase of up to 4.5 h and a post-treatment period which will commence with the administration of the first dose of study drug and will continue for at least 4 h and up to a maximum of 24 h.

### Outcomes and endpoints

The primary efficacy endpoint is time to response measured during the first 2 h after the first dose. Response is defined as a CGI-I score of 1 (very much improved) or 2 (much improved). Secondary endpoints will include: the proportion of patients achieving response at 10, 20, 30, 50, 60, 90 and 120 min after the first dose of study drug; the total number of patients who receive 1 or 2 doses of study drug without rescue medication by 4 h and 24 h after the first dose of study drug; time to rescue medication; time to the second dose of study drug; and satisfaction with study drug (evaluated using Item 14 of the Treatment Satisfaction Questionnaire for Medication [TSQM]; [24]). Safety and tolerability will also be assessed through the reporting of adverse events, physical examination, recording of vital signs.

### Statistical analysis

The primary endpoint “time to response” is defined as the first time point in minutes after Dose 1 at which CGI-I score of 1 or 2 is achieved during the 120 min after the first dose. The comparison of time to response between the two treatment groups will be performed using a Wilcoxon rank-sum test with a two-sided significance level of 0.05. Patients without response within 2 h will be considered as non-responders and the ‘time to response’ as 4 h (2 h more than the maximum follow-up for this variable). The median difference (95% CI) will be estimated by means of the Hodges-Lehmann approach based on the Wilcoxon rank-sum (Mann-Whitney) distribution. Kaplan-Meier curves of time to response will also be presented by treatment group. Additionally, the Mantel-Haenszel log-rank test will also be conducted for sensitivity purposes.

Secondary analyses will be exploratory without formal sample size estimation. Safety and tolerability data will be presented descriptively.

A total sample size of 180 in each group will have approximately 90% power to demonstrate superiority of inhaled loxapine versus IM aripiprazole for the primary efficacy endpoint at a one-sided significance level of 0.025. If the interim analysis suggests that more than 30% additional patients are required at 0.025 one-tailed alpha level and approximately 90% power, it will be considered if it is feasible to include >30% additional patients. Since there will be neither stopping for overwhelming efficacy, nor is there a situation where the sample size will decrease based on the interim analysis results, the alpha level will be preserved.

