REMS (Risk Evaluation and Mitigation Strategy) is necessary with inhaled loxapine to mitigate the risk of bronchospasm. For this reason, only the centers with immediate access on site to supplies and personnel trained to manage acute bronchospasm will participate in this study. REMS is the strategy to manage a known or potential serious risk associated with a drug or biological product required by the US FDA (Food and Drug Administration).

The pharmacokinetic profiles (PK) of both drugs differ significantly and this is explained by the differences in the administration route. The peak plasma concentration of IM aripiprazole is achieved at 1 h, while for inhaled loxapine it is 2–3 min. Such a short time is explained by the fact that inhaled loxapine is directly absorbed into the blood stream with a PK profile similar to IV formulations. This study will prove if these differences in PK parameters correspond to clinical parameters, namely shorter time to response of inhaled loxapine.

Patients will be randomly assigned to treatment to avoid bias in terms of treatment allocation. The delivered treatment is necessarily open-label due to the different methods of administration. To avoid the issue of rater bias, drug administration and clinical evaluation will be carried out by different personnel, with the clinical rater blinded to treatment allocation and the randomization will be stratified by diagnosis to balance the groups. Patients will be instructed not to tell the treatment they receive.

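### Randomisation is stratified by diagnosis, but the named primary test and interval are unstratified: valid, but power is lost if diagnosis predicts time to response

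*Protocol article*

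**What the plan says.** On allocation, the Protocol article (Methods, Study treatments) states that randomisation "will be stratified according to the patient’s disease type (schizophrenia or bipolar I disorder". The Discussion gives the reason: "the randomization will be stratified by diagnosis to balance the groups".

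On the primary analysis (Methods, Statistical analysis): "The comparison of time to response between the two treatment groups will be performed using a Wilcoxon rank-sum test", at a two-sided level of 0.05. The median difference and its 95% CI come from the "Hodges-Lehmann approach based on the Wilcoxon rank-sum (Mann-Whitney) distribution". No stratum is attached to either.

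For sensitivity, "the Mantel-Haenszel log-rank test will also be conducted for sensitivity purposes". The article does not say whether this test is stratified.

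On size, "A total sample size of 180 in each group will have approximately 90% power", at one-sided 0.025. No effect size, response-time distribution or diagnosis mix is given, and the Design section says that CGI-I data for the first two hours are scarce.

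**The concern.** The design treats diagnosis as important enough to control at allocation, and the primary analysis then leaves it out. This is not a detail left for the analysis plan to fill in. The article names a specific two-sample test and an interval tied to it, and a stratified rank test is a different procedure.

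Balancing the arms within diagnosis removes between-diagnosis variation from the treatment contrast. The unstratified rank-sum variance still counts that variation. If diagnosis predicts speed of response, the standard error is too large for the design, and the test rejects less often than it should under both the null and the alternative. What is at stake is efficiency, not validity. It deserves a sentence here because the sponsor describes the sample size as hard to estimate and plans to revisit it at the interim analysis.

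**Working it through.** **The plan's own figure.** The 90% power cannot be reproduced forward, because no effect size is stated. It can only be inverted. Noether's formula is N = (z_α + z_β)² / [12·c(1−c)·(p − 0.5)²]. With N = 360, c = 0.5, z_α = 1.960 and z_β = 1.282, (p − 0.5)² = 10.51 / (3 × 360) = 0.00973, so p ≈ 0.599. That is the probability of faster response on loxapine that the stated power would imply. The calculation neither confirms nor refutes the 90%.

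**Inputs from the article.** 180 per arm; 1:1 allocation stratified by diagnosis; ratings at 10, 20, 30, 50, 60, 90 and 120 min; non-responders tied at the worst value; critical value 1.96 (two-sided 0.05, equivalent to one-sided 0.025).

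**Assumptions not in the article.** Exponential response times with a median of about 50 min; treatment rate ratio 1.485, chosen to give Wilcoxon power near 89% when diagnosis is not prognostic; diagnosis split 50:50 or 70:30; diagnosis rate ratio 1 to 3; exact balance within diagnosis.

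**Tests compared.** Let U_h and V_h be the centred rank sum and its tie-corrected variance in stratum h, of size N_h.
- Unstratified Wilcoxon: Z = U/√V on pooled ranks.
- Van Elteren: Z = Σw_hU_h / √(Σw_h²V_h), with w_h = 1/(N_h + 1).

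**Results** (20,000 simulated trials per setting; Monte Carlo standard error about 0.2 points for power and 0.0015 for alpha):

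| Split | Diagnosis rate ratio | Control response by 2 h, by stratum | Wilcoxon power | Van Elteren power | Loss (points) | Two-sided alpha, Wilcoxon |
|---|---|---|---|---|---|---|
| 50:50 | 1 | 81% / 81% | 88.6% | 88.4% | −0.2 | 0.050 |
| 50:50 | 1.25 | 84% / 77% | 88.5% | 88.7% | 0.2 | 0.049 |
| 50:50 | 1.5 | 87% / 74% | 87.7% | 88.3% | 0.6 | 0.048 |
| 50:50 | 2 | 90% / 69% | 85.8% | 88.0% | 2.3 | 0.044 |
| 50:50 | 3 | 94% / 62% | 81.3% | 87.4% | 6.1 | 0.031 |
| 70:30 | 1.5 | 85% / 71% | 88.2% | 88.7% | 0.5 | 0.048 |
| 70:30 | 2 | 87% / 64% | 86.2% | 88.0% | 1.8 | 0.045 |
| 70:30 | 3 | 90% / 54% | 83.4% | 87.4% | 3.9 | 0.034 |

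Losses are taken from unrounded powers.

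**Analytic check of the conservatism.** If a share s of the pooled rank variance lies between diagnoses, the actual two-sided alpha is about 2[1 − Φ(1.96/√(1 − s))]. Under the same 50:50 assumptions s is 0.028, 0.079 and 0.181 at ratios 1.5, 2 and 3, giving alpha of 0.047, 0.041 and 0.030. The simulated values are 0.048, 0.044 and 0.031.

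**A different model.** A proportional-odds simulation (60:40 split, treatment odds ratio 1.82, 4,000 runs) gives 89.8% unstratified against 89.7% stratified when diagnosis has no effect, 89.2% against 90.3% when diagnosis shifts the odds 2.2-fold, and 85.7% against 88.4% at 3.3-fold. The direction is the same and the size similar.

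**Log-rank, for whichever form is intended.** Under the exponential model at 50:50, unstratified against stratified power is 93.0% against 93.0% at ratio 1, 92.2% against 93.1% at 1.5, 90.0% against 92.9% at 2, and 83.9% against 92.3% at 3.

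**The case against.** The strongest reply is that nothing is invalid. The unstratified test keeps type I error at or below its nominal level apart from simulation error, stratified allocation achieves the stated aim of balance whatever test follows, and the interim sample-size re-calculation could absorb a small shortfall. The first two points stand. The third is true but pays for the shortfall in patients, when a change of test would avoid it.

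Three stronger readings are tempting, and the article supports none of them.

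- **That power is certainly being lost.** This requires diagnosis to predict time to response. The article neither says so nor gives a figure, and choosing diagnosis as a stratification factor does not establish it. If diagnosis is not prognostic there is no loss, and up to a rate ratio of 1.5 the loss is under 1 point. The 4 to 6 point losses need a large contrast, such as control response by 2 h of 94% in one diagnosis and 62% in the other.
- **That the log-rank test is unstratified.** The article names the test and is silent on strata. In a condensed article, that detail may sit in the full protocol or the analysis plan, so silence is not a statement that strata are ignored.
- **That the stated 90% power is wrong.** It cannot be checked without the effect assumption, and nothing above contradicts it.

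**Conclusion.** The mismatch is real but minor. The primary test and interval, as named, omit the randomisation factor. The consequence is conditional: conservatism and some loss of power if diagnosis is prognostic, with the sizes shown above resting on assumed exponential response times, an assumed diagnosis mix and exact balance within strata. The trial's conclusion is not threatened.

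The case for changing rests on asymmetry. Under these assumptions the most that stratifying cost was 0.2 points, within simulation error, and the most it gained was about 6.

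**What to change.** In Statistical analysis, and in the analysis plan before any treatment comparison is seen:

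1. Make the primary test the van Elteren (stratified Wilcoxon) test, with disease type as randomised (schizophrenia or bipolar I disorder) as the stratum and weights 1/(N_h + 1).
2. Base the effect estimate and its 95% CI on within-stratum comparisons, using a stratum-aligned Hodges-Lehmann estimate, so that test and interval correspond.
3. State that the log-rank sensitivity test is stratified by the same factor.
4. Use the same stratified test in the interim re-calculation of sample size.

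The cost is a few sentences and a change of procedure in the analysis program. No extra data, visits or patients are needed, because diagnosis is already recorded for randomisation.

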**Methods:**

The efficacy of inhaled loxapine and the alternative antipsychotic aripiprazole delivered via intramuscular (IM) injection will be compared in the Phase IIIb PLACID study. Adults (18–65 years) with a confirmed diagnosis of schizophrenia or bipolar I disorder presenting with acute agitation will be randomly assigned to open-label treatment in a 1:1 ratio. Clinical evaluation will be conducted by raters blinded to treatment assignment. The primary efficacy endpoint is time to response (defined as a Clinical Global Impression of Improvement [CGI-I] score of 1 [very much improved] or 2 [much improved]).

Secondary endpoints will include the percentage of responders at different time points after dosing; the proportion of patients who receive 1 or 2 doses of study drug; time to second dose; time to rescue medication; satisfaction with study drug (evaluated using Item 14 of the Treatment Satisfaction Questionnaire for Medication); and safety and tolerability. Approximately 360 patients will be recruited with an interim analysis conducted once 180 patients have completed the study to decide whether to stop for futility or continue with or without an increase in the sample size up to additional 288 patients.

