### Patients

The study population will consist of patients meeting DSM-5 criteria for schizophrenia or bipolar I disorder experiencing an acute episode of agitation, both hospitalized and attending to a psychiatric or general emergency room.

To be eligible to participate patients must be clinically agitated at baseline with a value ≥4 for the Clinical Global Impression of Severity (CGI-S; [23]) scale and otherwise in good health. Patients will be specifically excluded from participation if their agitation is judged to be caused primarily by acute alcohol or drug intoxication/withdrawal. Those patients judged to be at serious risk for suicide will also be excluded. Patients treated with benzodiazepines or other hypnotics or oral or short-acting IM antipsychotics within 1 h prior to study drug administration will be excluded although those patients may be subsequently reassessed for inclusion. Other exclusion criteria will include pregnancy or breastfeeding, a history of or current significant hepatic, renal, gastroenterologic, respiratory, cardiovascular, endocrinologic, neurologic or haematologic disease as well as acute or active airways disease.

All patients will be required to provide written informed consent prior to undergoing any study procedure. Patients considered by appropriately qualified staff to be of impaired capacity to provide informed consent will not be eligible for participation. In Spain a proxy or deferred informed consent is possible. If patients have recovered the capacity, they will be asked to provide the informed consent; otherwise the data will not be used in the analysis.

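### The primary Wilcoxon test is valid but leaves out baseline CGI-S, which forgoes some precision if CGI-S is related to time to response

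*Protocol article*

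**What the plan says.** All of this is in the protocol article.

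- **Primary test** (Statistical analysis): "The comparison of time to response between the two treatment groups will be performed using a Wilcoxon rank-sum test". The level is two-sided 0.05. The effect estimate is a Hodges-Lehmann median difference with a 95% CI taken from the same rank-sum distribution. No covariate or stratum is named for either.
- **Sensitivity test** (same section): "Additionally, the Mantel-Haenszel log-rank test will also be conducted for sensitivity purposes". Again no covariate is named.
- **Non-responders** (same section): "Patients without response within 2 h will be considered as non-responders and the ‘time to response’ as 4 h", so they share the worst rank.
- **Sample size** (same section): "A total sample size of 180 in each group will have approximately 90% power to demonstrate superiority". The alpha for this calculation is one-sided 0.025. No effect size, median or response rate is given.
- **Baseline severity** (Patients): "patients must be clinically agitated at baseline with a value ≥4 for the Clinical Global Impression of Severity" scale. Table 1 marks CGI-S in the baseline column only, and Study treatments puts baseline evaluations within 30 min before the first dose.
- **Randomisation** (Study treatments): stratified by disease type. CGI-S is not a stratification factor.

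**The concern.** CGI-S is an entry condition, so every eligible patient has a pre-dose severity rating from the same family of scales as the outcome. Under the stated primary analysis it serves for eligibility and then drops out. A baseline variable that is related to the outcome can reduce the residual variance of the comparison without adding patients.

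That would be useful here. The Design section admits that sparse early CGI-I data make the sample size hard to estimate, and the Abstract allows an increase of up to 288 patients after the interim analysis. Since randomisation does not balance CGI-S by design, a prespecified adjustment would also answer, more convincingly than a post hoc one, the objection that one arm happened to start less agitated.

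**Working it through.** **1. The plan's own figure.** The 360 patients cannot be reproduced because no effect size is stated. The implied effect can be back-solved with Noether's formula for the rank-sum test. The inputs are N = 360, 1:1 allocation (c = 0.5), power 0.90 and one-sided alpha 0.025, which has the same critical value, 1.96, as two-sided 0.05.

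(P − 0.5)² = (1.96 + 1.2816)² / (12 × 0.5 × 0.5 × 360) = 10.508 / 1080 = 0.00973

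So P − 0.5 = 0.0986, and the implied probability of a faster response on loxapine is about 0.599. On a latent normal scale this is √2 × z(0.5986) ≈ 0.353 SD.

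**2. Effect of adjustment.** Let r be the correlation between baseline CGI-S and the ranked time to response. The article gives no value, so r is an assumption. Adjustment multiplies the residual variance by (1 − r²):

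- power at 360 = Φ(3.2415 / √(1 − r²) − 1.96)
- total needed for 90% power = 360 × (1 − r²), rounded up
- patients' worth = 360 × r²

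| Assumed r | Power at 360 | Total for 90% | 360 × r² | Cut in SE |
|---|---|---|---|---|
| 0 | 90.0% | 360 | 0 | 0% |
| 0.1 | 90.3% | 357 | 3.6 | 0.5% |
| 0.2 | 91.1% | 346 | 14.4 | 2.0% |
| 0.3 | 92.5% | 328 | 32.4 | 4.6% |
| 0.4 | 94.3% | 303 | 57.6 | 8.3% |
| 0.5 | 96.3% | 270 | 90.0 | 13.4% |

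**3. Simulation on the tied endpoint.** There were 3,000 runs per setting with 180 per arm, seven visit times and one tied class of non-responders. Three inputs are assumptions: CGI-S levels 4 to 7 in proportions 35/40/20/5%, control response accumulating to 73% by 120 min, and an effect of 0.36 latent SD.

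| Latent r (realised correlation) | Wilcoxon | Rank ANCOVA | van Elteren by CGI-S |
|---|---|---|---|
| 0 (0.00) | 0.897 | 0.897 | 0.895 |
| 0.1 (0.095) | 0.908 | 0.912 | 0.908 |
| 0.2 (0.186) | 0.898 | 0.908 | 0.904 |
| 0.3 (0.282) | 0.898 | 0.921 | 0.917 |
| 0.5 (0.471) | 0.903 | 0.963 | 0.965 |

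The formula at the realised correlations 0.186 and 0.282 gives about 91.0% and 92.2%, against 90.8% and 92.1% simulated for rank ANCOVA. A separate simulation (4,000 runs per setting, slightly different assumed distributions) gave 91.4%, 92.5% and 93.5% at rank correlations 0.21, 0.30 and 0.39.

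**4. Validity of the stated test.** With no treatment effect, the unadjusted Wilcoxon test rejected in 0.045 to 0.058 of runs across all settings, against a nominal 0.05. The standard error at 3,000 runs is √(0.05 × 0.95 / 3000) = 0.004. The 0.058 is about two standard errors high, but rank ANCOVA and van Elteren gave 0.057 and 0.056 on the same data sets, so it reflects the draws and not the lack of adjustment.

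**5. Chance imbalance.** With 180 per arm, the 95% range of the difference in mean CGI-S is ±1.96 × √(2/180) = ±0.207 SD. At that limit the outcome shifts by r × 0.207: 0.021 SD at r = 0.1, 0.062 SD at r = 0.3 and 0.103 SD at r = 0.5. Against the implied 0.353 SD these are about 6%, 18% and 29%.

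**The case against.** The strongest reply is that nothing is wrong with the stated test: a two-sample Wilcoxon test is a valid, prespecified comparison in a randomised trial. That stands. A reader might infer that leaving CGI-S out biases the result or inflates type I error. The documents do not support this, because the null distribution of the test already allows for random imbalance, and step 4 shows nominal rejection rates. Chance imbalance is a matter of conditional precision.

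A reader might also infer that precision is certainly being lost. That needs a correlation the article does not give. It could be low, because CGI-I is an improvement score that already refers back to the starting state, and because entry at CGI-S 4 or more narrows the range. Its sign is open too, although adjustment gains from either sign. At r = 0.1 the gain is negligible.

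The change also has a cost. The Hodges-Lehmann interval belongs to the unadjusted rank-sum distribution, and the Abstract frames success as a shorter median time to response. A rank analysis of covariance yields no matching estimate in minutes, so test and interval could disagree slightly. This stands and has to be handled in the fix.

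Finally, a supportive CGI-S-adjusted analysis may exist in the full protocol or the SAP, neither of which is shown. Its absence from the article is therefore no finding. What can be commented on is the primary test, which the article does fix.

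**Conclusion.** The point holds as an efficiency improvement to a valid primary analysis. If CGI-S is related to time to response, the stated test forgoes some precision and does not condition on a chance difference in severity. The gain is about one power point or less for r up to 0.2, about 2.5 points at 0.3 and about 4 at 0.4. At r = 0 there is no material loss: 0.897 for both tests in one simulation, 89.7% and 89.8% in the other.

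These figures rest on the assumed correlations, on the back-solved effect and, for the simulations, on assumed CGI-S and response distributions. Severity is low. Confidence is high on what the article states and moderate on the size of the gain.

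**What to change.** Before any interim data are seen:

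1. Prespecify as the primary test a rank-based comparison adjusted for baseline CGI-S. This can be a rank analysis of covariance (Quade, or Koch's covariance-adjusted Wilcoxon) or a van Elteren test stratified by CGI-S level. Keep two-sided 0.05 and keep non-responders ranked worst.
2. Use the same test in the interim calculation and sample size re-estimation.
3. Keep the unadjusted Wilcoxon test as a sensitivity analysis.
4. Keep the Hodges-Lehmann median difference with its 95% CI as the estimate in minutes, and state that it is unadjusted and may not agree exactly with the adjusted p-value.

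The change needs a few sentences in the statistics section and the SAP, with no new data and no extra patients. The downsides are a less familiar primary test and the possible small mismatch in item 4.

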**Discussion:**

The PLACID trial will assess the efficacy and safety of inhaled loxapine with deep lung absorption compared with the IM antipsychotic, aripiprazole, in acutely agitated patients with schizophrenia or bipolar disorder. In the event that the median time to response of inhaled loxapine is significantly shorter than that of the intramuscular aripiprazole, the PLACID study has the potential to support the inhaled antipsychotic therapy as the standard of care in this setting.

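### The Hodges-Lehmann 'median difference' does not estimate the difference in medians named in the abstract, and at about the planned effect its upper confidence limit will usually be exactly 0 min when the Wilcoxon test is significant

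*Protocol article*

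**What the plan says.** Protocol article, Statistical analysis: the primary variable is "defined as the first time point in minutes after Dose 1 at which CGI-I score of 1 or 2 is achieved" within 120 min. For the rest, "Patients without response within 2 h will be considered as non-responders and the ‘time to response’ as 4 h". The comparison is a "Wilcoxon rank-sum test with a two-sided significance level of 0.05", and the effect estimate is given as "The median difference (95% CI) will be estimated by means of the Hodges-Lehmann approach based on the Wilcoxon rank-sum (Mann-Whitney) distribution". Kaplan-Meier curves by group and a log-rank sensitivity test are also planned.

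Outcomes and endpoints gives the rating times as "at 10, 20, 30, 50, 60, 90 and 120 min after the first dose of study drug". Table 1 shows the same CGI-I times within the first 2 h, with windows of ±2 min up to 50 min and ±5 min from 60 to 120 min.

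The Discussion paragraph of the abstract says what a positive result would support: "In the event that the median time to response of inhaled loxapine is significantly shorter than that of the intramuscular aripiprazole".

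**The concern.** Two things do not fit together.

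- **The quantity.** Hodges-Lehmann estimates the median of all differences between a loxapine patient and an aripiprazole patient. It equals the difference in medians only under special conditions, such as a pure shift of one distribution against the other. A shift would have to move the rating times and the assigned 240 min, and both are fixed in each arm. A significant Wilcoxon test shows that one arm tends to respond sooner. It does not show that its median is shorter. Neither procedure supports the abstract's sentence as worded.
- **The behaviour with ties.** With eight values, many pairwise differences are exactly 0. The estimate and its limits can fall inside that block of zeros.

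At stake is how the main result reads. A positive trial could be reported with a confidence limit of 0 min, or an estimate of 0 min, although the test is clear.

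**Working it through.** **The plan's own figure.** The article states about 90% power with 180 per group at one-sided 0.025, but gives no effect size or response-time distribution, so the power cannot be reproduced. Solved backwards with Noether's formula for 360 patients in equal arms:

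P = 0.5 + √[(1.960 + 1.282)² / (3 × 360)] = 0.5 + √(10.51 / 1080) = 0.599.

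P is the probability that a loxapine patient responds sooner, with ties counted one half. The planned effect is therefore about P = 0.60.

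**Possible values.** 10, 20, 30, 50, 60, 90, 120 and 240 min: eight, if scheduled times are analysed.

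**Where the limits fall.** There are 180 × 180 = 32,400 pairs. Let A be the pairs in which the loxapine patient is sooner and T the tied pairs. Using the normal approximation without tie correction:

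- SD of the rank-sum statistic: √(32,400 × 361 / 12) = 987. Critical count: 16,200 + 1.96 × 987 = 18,135, or 0.5597 of all pairs.
- Test significant for loxapine: A + T/2 > 18,135.
- Upper limit below 0: A alone must reach about 18,135.
- Upper limit above 0: A + T < 18,135. This is impossible when the test is significant, since A + T ≥ A + T/2. The limit can touch 0 but not cross it.
- Estimate exactly 0: A < 16,200 while A + T > 16,200.

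With tie share t = T/32,400 and A/32,400 = P − t/2, the upper limit is below 0 only if t < 2(P − 0.5597). The estimate is 0 if t > 2(P − 0.5).

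| Observed P | Limit is 0 if tie share exceeds | Estimate is 0 if tie share exceeds |
|---|---|---|
| 0.60 | 8.1% | 20% |
| 0.65 | 18.1% | 30% |
| 0.70 | 28.1% | 40% |

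If both arms had the same distribution over eight values, the tie share would be at least 1/8 = 12.5%. Arms that differ modestly should lie near or above this, so it is a guide, not a strict bound. It exceeds 8.1% and is below 18.1%.

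**Simulation.** The response-time profiles are assumptions, since the article gives none: mainly grouped Weibull times, some with an 80% ceiling on response.

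| Setting | Significant trials with upper limit reaching 0 |
|---|---|
| Scheduled times, 180 per arm, about 90% power | 75–94% in one set, 79–99.8% over 30 scenarios |
| Same, P = 0.65 | 13–68% |
| Same, P = 0.70 | 0–7% |
| 324 per arm ((360 + 288)/2), P = 0.60 | 64–99.9% |

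At about the planned effect the estimate was exactly 0 in 5–87% of significant trials, depending on the profile. Hodges-Lehmann differed from the difference in sample medians in 42–100% of them. With an aripiprazole latent median of 60 min, shape 1.2 and no ceiling, typical values were −10 min and −35 min. Where few patients respond, a group median can fall on the assigned 240 min: the median difference was then −150 min and the Hodges-Lehmann estimate 0.

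**Actual minutes.** Clock times within the windows break most ties but not those at 240. Three further profiles (power 84–92%) show this:

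| 2-h response, loxapine / aripiprazole | Pairs tied at 240 | Limit reaching 0, scheduled times | Limit reaching 0, actual minutes |
|---|---|---|---|
| 87% / 80% | 0.13 × 0.20 = 2.6% | 79% | 23% |
| 75% / 66% | 0.25 × 0.34 = 8.5% | 90% | 65% |
| 64% / 52% | 0.36 × 0.48 = 17.3% | 99.5% | 96% |

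Other runs with actual minutes gave 6–41% and 11–69%, and 86–100% with an 80% ceiling on response.

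**The case against.** The strongest reply is that the decision rule is untouched. The Wilcoxon test decides superiority, and its validity, alpha and power do not depend on the estimate reported beside it. This stands. It is why the point concerns reporting and is not a fault in the primary test.

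A reader might infer that a positive trial would contradict itself. The documents do not support that. After a significant test the limit equals 0 and never exceeds it, so direction and decision agree. What remains is an awkward display and, in some profiles, an estimate of 0 min.

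A reader might also take the touching limit as certain. It is not. It depends on the effect, the response rate and the time basis. The article speaks of a first time point, which reads as scheduled times, but it does not rule out actual minutes.

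Other outputs are planned: Kaplan-Meier curves, the log-rank test, and "the proportion of patients achieving response at 10, 20, 30, 50, 60, 90 and 120 min after the first dose of study drug". Hodges-Lehmann would not be read alone, but none of these is stated as a between-group estimate with an interval for the primary endpoint.

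The median wording is one conditional sentence in the abstract. The body's Discussion already speaks of shorter time to response. That makes the correction small, but the sentence still promises something that neither procedure tests. Finally, Hodges-Lehmann is the usual companion of the Wilcoxon test and tie handling may be set out in the analysis plan. The choice and its label, however, are fixed in the article.

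**Conclusion.** The point holds as a should-fix. That Hodges-Lehmann is not the difference in medians here, and that the Wilcoxon test is not a test of medians, follows from the fixed grid and the assigned 240 min and needs no simulation.

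The interval problem is conditional. With scheduled times, 180 per arm and P of about 0.60, an upper limit of exactly 0 min accompanies roughly 75–99% of significant tests. It shrinks at P of 0.65 or more and has almost gone at 0.70. Actual minutes usually reduce it, but it can stay high when many patients do not respond. These rates rest on assumed response-time profiles.

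**What to change.** - Keep the Wilcoxon test. Report with it the Mann-Whitney probability that a loxapine patient responds sooner, ties counted one half, with its 95% CI, as the effect measure that matches the test.
- If Hodges-Lehmann is kept, label it as the median of pairwise differences and say that it is not the difference in medians.
- In the Discussion paragraph of the abstract, replace median time to response with time to response.
- If the analysis plan does not already do so, state whether scheduled or actual minutes are analysed.
- For description in minutes, give Kaplan-Meier medians by arm and, optionally, the restricted-mean difference over 0–120 min. The latter should stay supplementary: it values non-responders at 120 instead of 240, and in the three profiles with stated 2-h response rates it agreed with the Wilcoxon decision in 95–97% of trials, not all.

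Cost: one extra table row, a few words, and an effect measure that is not in minutes. No new data are needed, and the test and sample size do not change.
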